### Secondary outcomes

The following psychological measures will be collected at baseline (T1), and after 1 month (T2), 3 months (T3), and 6 months (T4) from treatment beginning.

Questionnaires will be administered by a clinical psychologist working in the clinic and independent from the study.

The *Questionnaire of Evaluation of Perceived Competence in Adherence to CPAP in OSAS* (CEPCA; Rudilla et al., 2021a) will be used to assess the participants’ perceived self-efficacy. It comprises 13 items grouped into three categories: knowledge of OSAS and its associated risk; expectations regarding CPAP treatment; and confidence in overcoming barriers associated with the use of the device. The scores obtained in the CEPCA are positively related to the quality of life and motivation and negatively related to daytime sleepiness.

The participants’ perceived quality of life will be assessed using the *Visual Analogical Well-being Scale for apnea* (Masa et al., 2011).

Moreover, the individuals’ motivation will be assessed according to the Prochaska and Di Clemente transtheoretical model of change Prochaska and DiClemente (1982). Based on the answer to a single question [“What is the level of motivation that motivates you to undertake CPAP therapy? This includes a 5-point Likert response scale (none, a little, somewhat, motivated, very motivated)?”] each patient will be classified as in the: pre-contemplation (no motivation), contemplation (low motivation), determination (some motivation), action (quite motivated), or maintenance (high motivation) motivational stage.

## Procedure

Socio-demographic (age, level of studies, presence of caregiver at home), psychological (motivation and perceived competence) clinical variables (somnolence and apnea-hypopnea index), and variables concerning the time the patient spends from home to the care center and the confidence in using electronic applications will be used to classify patients’ adherence to treatment as low, moderate or high, and to create a tailored motivational treatment plan for the subjects assigned to the experimental group. Patients showing low adherence will receive a more intensive care plan, than those recognized as highly compliant with CPAP use. The results are patients with the “a” profile (characterized by autonomy and mobility, predisposition to remote-controlled follow-up), patients with the “b” profile (need for more intensity in follow-up), or patients with the “c” profile (more difficulties to move around and require more intensive treatment). Profile “d” was applied to patients who were professional drivers, as they require specific interventions based on their occupation (see Rudilla et al., 2021b).

Participants assigned to the control group will receive a usual pulmonary rehabilitation program for patients with OSAS receiving CPAP therapy, which is a standard technical training comprising information regarding the use, maintenance and safety measures of the device, plus a home inspection delivered by a technician who has the only task of doing maintenance to the machinery.

In addition, subjects in the MotivAir group will follow a telephone-based intervention—lasting ~45 min—based on MI principles and techniques delivered by a nurse. For the specific purpose of the study, the nurse will preliminarily receive 8 h of MI training provided by two psychologists experts in the MI approach (authors GR and GP). During the training, the nurse will learn about the collaborative, evocative, and client-centered spirit of MI, and the characteristics that define each stage of change and will be instructed to apply the basic communication and listening skills of this approach (open-ended questions, affirmations, reflective listening, summarizing). Then she will learn to reinforce and elicit change talk, while also responding in ways that reduce counter-change talk and to roll with the patients’ inner resistance to change by affirming the patients’ autonomy and reflecting their resistant speech with empathy. Next, the issues of how and when to introduce the development of a change plan, and enhance the individuals’ commitment to change will be addressed.

The treatment plan will be implemented based on each patient’s level of adherence. To low adherence (score below 16 on the ESS and CEPCA questionnaires) a more intensive telephone-based assistance (days 1, 8, 16, 30, 90, 120, 180 from the end of the rehabilitation period) will follow. In the case of high adherence (score greater than or equal to 16 on the ESS and CEPCA questionnaires), phone encounters will be set on days 1, 8, 30, 90, and 180 after treatment termination.

At 1-, 3- and 6-month follow-up, adherence to the device will be assessed by automatedly recorded CPAP usage (hours/night) and AHI. Changes in the selected psychological variable will be also examined.

## Treatment fidelity

MI sessions were audio-recorded, transcript verbatim, and—some of them—randomly selected to be critically supervised by an expert in the field not involved in the study (Martino et al., 2008).

## Statistical analysis

Descriptive statistics (means ± SD, or median and interquartile ranges, as appropriate) will be used to describe the study sample with regard to baseline characteristics. Before selecting the most appropriate statistical tests, assumptions for parametric analyses will be checked. Continuous variables will be reported as mean and standard deviation (or median and interquartile range when needed). Categorical variables will be reported as absolute and relative frequency. The mean daily apnea hour will be compared between groups by repeated-measures analysis of variance. To account for the correlation of within-patient measurements, a linear mixed model with a covariance variance matrix chosen based on the lowest Akaike Information Criterium (AIC) index value will be used. The model will also possibly include some characteristics of patients that are found to influence the level of expected adherence identified with preliminary multinomial logistic regressions. All tests will be two-tailed and the *p*-value will be significant if less than 0.05. Analyses will be conducted with SPSS statistical software.

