**Methods:**

A multicenter randomized controlled trial (RCT) design with random allocation at the level of the individual will be conducted to compare the impact of the experimental program (usual care *plus* MI) with a control group receiving usual care only in improving selected clinical and psychological parameters in the patients. A minimum sample of 80 participants (40 patients per group) will be recruited in each center according to the inclusion criteria. After the initial screening, participants will be randomly assigned to either the experimental group or the control condition. The program will last 180 days and will be delivered by a trained nurse. The impact of the MotivAir program on selected primary (adherence to CPAP in terms of average hours of usage per night and the Apnea-Hypopnea Index, AHI) and secondary (motivation, perceived competence, quality of life, sleepiness) outcomes will be measured at baseline, and after 1-, 3-, and 6-month from CPAP initiation.

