## Introduction

Obstructive sleep apnea syndrome (OSAS) is a chronic illness characterized by a complete or partial obstruction of the upper airway. It has been demonstrated to be a risk factor for several diseases—including hypertension, impairment of cognitive functions, ischemic heart disease, and stroke (Garvey et al., 2015)—and to be correlated with other non-medical consequences—such as work-related injury, and motor vehicle crash (Garbarino et al., 2015, 2016)—that increase OSAS’s clinical and economic burden. Also, persons with OSAS often exhibit a poor health-related quality of life (HRQoL) (Lo Bue et al., 2020), which has a demonstrated negative impact on physical health outcomes (e.g., negative health perceptions, increased bodily pain, and poor physical functioning) and psychosocial functioning (e.g., mood disturbance, poor academic performance, and reduced social life) of individuals with OSAS (Timkova et al., 2020). In Italy, despite the impact of OSAS is highly underestimated due to substantial diagnosis gaps—it affects 27% of the adult population, of which 65% are males (Armeni et al., 2019).

Continuous positive airway pressure (CPAP) is the first-line treatment for moderate/severe OSAS. It increases the individuals’ clinical parameters and HRQoL by eliminating daytime sleepiness, and also decreases morbidity and mortality rates related to cardiovascular diseases (Luyster, 2017; Morsy et al., 2019; Lo Bue et al., 2020). Still, the effectiveness of the device is often limited by suboptimal adherence (Gay et al., 2006; Giles et al., 2006). Indeed, it has been suggested that improvements are more consistent with over 5.5 h of usage per night (Batool-Anwar et al., 2016; Bakker et al., 2019), but the literature reports that between 29 and 83% of patients enrolled in research studies use CPAP < 4 h per night (Bakker et al., 2016; Weaver, 2019) or refuse treatment (Baratta et al., 2018; Rezaie et al., 2021).

Adherence to CPAP treatment depends on several factors, including individual characteristics, features associated with the device (Crawford et al., 2014; Batool-Anwar et al., 2016) and its side effects, as well as psychological and social determinants (Crawford et al., 2014; Sanna and Lacedonia, 2018).

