Concerning the educational and formative aspects, Olsen et al. (2012) applied an educational program to naive patients that integrated the MI—which was recognized as best practice by the Agenzia di Tutela della Salute of Lombardy in Italy for the promotion of a healthy lifestyle—based on the work of Rollnick and Miller (1995) with the modifications indicated by Aloia et al. (2004) for OSAS patients.

For these reasons, we develop the MotivAir project—a phone-based motivational intervention that integrates telemedicine and telephone assistance based on MI principles and techniques to support adherence to CPAP in naïve patients with OSAS. This is the first study in Italy that will use MI-based intervention for OSAS patients by integrating telemedicine and telephone assistance and in-person sessions. Furthermore, it will be based on personalized care plans in response to the patient’s profile (e.g., patient age, socio-demographic variables, and distance to hospital) and this approach could identify who needs intensive care and further increase CPAP adherence. A personalized-based intervention represents a golden standard for the cost-effective impact, but only one study has been achieved with personalization of care for patients with OSAS using CPAP.

Rudilla et al. (2021b) already showed increased compliance with the device, as well as increased self-efficacy, and quality of life in terms of daily activities, and social relationships in CPAP-naive patients with severe OSAS after receiving a personalized motivational intervention plan. The purpose of this randomized controlled trial (RCT) will be to determine whether MI-based strategies delivered by a nurse, and added to a standard pulmonary rehabilitation program, will be superior to usual care in improving adherence to CPAP. Specifically, we hypothesize that adding MI feedback to standard care will result in improved adherence to CPAP in terms of average hours of usage per night and increased Apnea-Hypopnea Index (AHI) after 90 days from CPAP initiation. We also hypothesize that results will be maintained or increase at 6 months of follow-up and that patients will also show increased levels of motivation, perceived competence, and sleepiness.

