## Sample size calculation

A sample of 80 patients (40 in each group) will allow detection as a significant effect size of 0.67 (based on the average daily difference in apnea hours between groups) measured at the 6-month follow-up, a first type error of 0.05, a power of 80% and a drop-out of 10%. Data related to the effect size were retrieved from the PIMA study (Rudilla et al., 2021b), while the mean daily difference in apnea hours and the standard deviation were provided by the researchers. The sample size was assessed using PASS 14 software (Power Analysis and Sample Size Software (2015). NCSS, LLC. Kaysville, Utah, United States, ncss.com/software/pass).

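### The trial is sized on the 180-day difference, but the analysis section names a repeated-measures ANOVA and a mixed model without making the 180-day contrast the primary test

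*Protocol article*

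**What the plan says.** Three sections of the protocol article bear on this.

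- **Sample size calculation:** 80 patients, 40 per group, to detect an "effect size of 0.67 (based on the average daily difference in apnea hours between groups) measured at the 6-month follow-up", with type I error 0.05, 80% power and 10% drop-out.
- **Primary outcome:** mean CPAP hours per night and AHI at 180 days are primary. The 30-day and 90-day data are secondary.
- **Statistical analysis:** the groups are compared by repeated-measures ANOVA. To allow for within-patient correlation, "a linear mixed model with a covariance variance matrix chosen based on the lowest Akaike Information Criterium (AIC) index value will be used". Tests are two-tailed at 0.05. The section does not say which visits enter the model, how time is coded, or which term or contrast decides the trial.

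Two other places blur the schedule. The abstract says of the primary and secondary outcomes together, hours per night included, that "outcomes will be measured at baseline, and after 1-, 3-, and 6-month from CPAP initiation". The Procedure section has device-recorded usage assessed at 1, 3 and 6 months only. The Introduction states its main hypothesis at 90 days, with 6 months as maintenance.

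**The concern.** A repeated-measures ANOVA with two groups yields two tests involving group. The main effect asks whether the arms differ on average over the visits. The group-by-time interaction asks whether the difference changes between visits. The trial was sized for neither. The mixed model does not settle the matter. With visit as a factor and an arm-by-visit term it can give the 180-day contrast; without that interaction, its arm coefficient is again an average over visits.

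So the trial could be declared positive with no difference at its primary time point, or miss a real one there. With two methods and no named contrast, the choice can be made after the results are seen. A conventional repeated-measures ANOVA also drops any patient with a missing visit, including one who has a 180-day value but lacks a 30-day or 90-day value.

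**Working it through.** **Step 1. Reproduce the stated sample size.** Inputs from the protocol: d = 0.67, two-sided alpha 0.05, power 80%, drop-out 10%.

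- Normal approximation: n per arm = 2(1.960 + 0.842)² / 0.67² = 15.70 / 0.4489 ≈ 35.
- Two-sample t-test: 35.96, so 36 per arm.
- Drop-out: 36 / (1 − 0.10) = 40 per arm, 80 in total. This matches the stated figure exactly.
- Power of the t-test with 36 per arm and d = 0.67: 80.05%.

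The 80 therefore comes from a two-group comparison at a single visit, not from a repeated-measures calculation.

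**Step 2. Power of the terms the ANOVA tests.** The protocol gives no SD, correlation or time profile, so these are assumptions: unit SD at each visit, compound symmetry with correlation ρ from 0.5 to 0.7, visits at 30, 90 and 180 days, n = 36 per arm. Write δ₁, δ₂, δ₃ for the arm differences in SD units and δ̄ for their mean.

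- Main effect: standardized difference = δ̄ / √((1 + 2ρ)/3), tested as a two-sample t.
- Interaction: noncentrality λ = (n/2) Σ(δⱼ − δ̄)² / (1 − ρ), on 2 and 140 degrees of freedom.
- 180-day contrast: δ₃ alone, tested as a two-sample t.

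Worked example, late effect 0 / 0.33 / 0.67: δ̄ = 1.00/3 = 0.333. At ρ = 0.5 the main effect is 0.333/√0.667 = 0.408; at ρ = 0.7 it is 0.333/√0.8 = 0.373. The squared deviations sum to 0.2245, so λ = 18 × 0.2245/0.5 = 8.1 at ρ = 0.5 and 18 × 0.2245/0.3 = 13.5 at ρ = 0.7.

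| Profile (30 / 90 / 180 days) | Main effect, ρ 0.5 to 0.7 | Interaction, ρ 0.5 to 0.7 | 180-day contrast |
|---|---|---|---|
| Constant 0.67 / 0.67 / 0.67 | 93% to 88% | 5% | 80% |
| Growing 0.22 / 0.45 / 0.67 | 63% to 55% | 38% to 58% | 80% |
| Late 0 / 0.33 / 0.67 | 40% to 35% | 71% to 91% | 80% |
| Fading 0.67 / 0.33 / 0 | 40% to 35% | 71% to 91% | 5% |

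The first three rows share the same 180-day effect, yet the power of the ANOVA terms runs from 5% to 93%. In the last row there is no 180-day effect, and both ANOVA terms still reject well above 5%.

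**Step 3. The baseline wording.** The abstract puts hours per night among the outcomes measured at baseline. The Introduction says the program is meant "to support adherence to CPAP in naïve patients with OSAS", and usage before CPAP starts can only be zero. The Procedure section lists 1, 3 and 6 months. The abstract is the outlier; the Statistical analysis section mentions no baseline usage.

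**The case against.** The best defense is that a mixed model with visit as a factor does deliver the 180-day contrast, that the Primary outcome section already fixes 180 days, and that an article may leave the exact contrast to the analysis plan. This stands to a degree: it would be wrong to say the plan cannot test the 180-day difference. But the article does more than stay silent. It names the ANOVA as the between-group comparison, and that method's standard terms do not match the powered question. Nor is the mismatch always a loss: under a constant effect the main effect has more power than the 180-day contrast (88% to 93% against 80%). It answers a different question.

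Three stronger readings are tempting, and the document does not support them.

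- **That the model uses a zero baseline usage value.** Only the condensed abstract sentence suggests it, and that sentence covers AHI and questionnaires, which do have baselines. If a zero baseline were added, a constant effect would average to 0.67 × 3/4 = 0.50. The standard error shrinks by the same factor, so the main-effect test is unchanged.
- **That type I error is inflated to about 9%.** This needs both a zero baseline and a compound-symmetric covariance: the pooled variance is then 0.75 of the true one, and the critical value becomes 1.96 × √0.75 = 1.70. The plan selects the covariance by AIC, so this is not the error rate of the stated plan.
- **That patients who abandon CPAP are treated as missing.** No section says so. Usage is recorded by the device, which could supply zero-hour nights. The Introduction's "or refuse treatment" describes the literature, and the 10% drop-out is a sample size allowance, not a scoring rule.

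**Conclusion.** The concern holds in this form: the trial is sized on, and defines as primary, the 180-day difference, while the named ANOVA tests other quantities and the mixed model is given no primary contrast. Under the assumed profiles, a late 180-day effect of 0.67 SD is found by the main effect with 35% to 40% power instead of 80%, and a fading effect with no 180-day difference gives a significant interaction 71% to 91% of the time. These figures depend on unit SD, compound symmetry, ρ of 0.5 to 0.7 and 36 evaluable patients per arm; they show the size of the mismatch, not a forecast. I read the apnea hours of the sample size and analysis sections as CPAP hours per night, which the article does not say outright.

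The sample size arithmetic is sound. The baseline usage issue is a wording conflict in the abstract, and the scoring of usage after a patient stops CPAP is a clarification only.

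**What to change.** 1. Name one primary analysis: a linear mixed model on hours per night at 30, 90 and 180 days, with arm, visit, arm-by-visit and center (randomization is stratified by center). The primary test is the arm contrast at 180 days; the 30-day and 90-day contrasts are secondary.
2. Drop the repeated-measures ANOVA as a competing primary analysis.
3. AIC selection of the covariance may stay, provided no structural zero baseline enters as a repeated measure. Unstructured covariance is feasible as a candidate: three visits need 3 variances and 3 covariances.
4. Correct the abstract so that hours per night is not listed as measured before CPAP initiation, and reconcile the Introduction's 90-day hypothesis with the 180-day primary time point.
5. State how usage is scored after a patient stops CPAP: which nights count as zero hours and which as missing data.

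The cost is wording. No extra data are needed, and N stays at 80, with about 80% power at 36 per arm for d = 0.67. The one trade-off is that, if the effect is constant over time, the 180-day contrast has somewhat less power than the average over visits; that is the price of testing the declared endpoint.

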## Randomization procedure

Randomization will be stratified within each center through permuted randomized blocks. Randomization will take place after the baseline measurements (Figure 1).

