### Measures

*Demographic information* about age, gender, education, and civil status will be self-reported at baseline.

*Clinical variables* will be recorded during the initial visit with the physician and retrieved by the patients’ medical records by a clinical psychologist working in the clinic, independent from the study. They will include the (1) *Epworth Sleepiness Scale* (ESS; Johns, 1991; Vignatelli et al., 2003) as a measure of daytime sleepiness. Respondents will be asked to rate, on a 4-point scale (0–3), their usual chances of dozing off or falling asleep while engaged in eight different activities. The ESS score can range from 0 to 24. The higher the ESS score, the higher that person’s average daytime sleepiness; and the (2) *Apnoea-Hypopnea Index (AHI)*, which determines the presence and severity of OSAS.

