### Primary outcome

The primary outcomes of this study will be the participants’ *adherence to CPAP therapy* (mean hours/night) and the AHI score after 180 days from the treatment beginning. CPAP usage (hours/night) will be automatedly recorded by the device, while AHI will be measured by polysomnography during follow-up visits at the hospital.

Data will be also analyzed after 30 and 90 days of treatment as a secondary outcome.

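### The plan does not commit to adjusting the 180-day AHI comparison for baseline AHI, so a primary outcome may be analysed with less precision than data already in hand allow.

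*Protocol article*

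**What the plan says.** The Primary outcome section makes CPAP hours per night co-primary with the "AHI score after 180 days from the treatment beginning"; the 30- and 90-day values are secondary.

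AHI is available before allocation. The Measures section lists it among the clinical variables that "will be recorded during the initial visit with the physician". The Abstract (Methods) says of the primary and secondary measures that "outcomes will be measured at baseline, and after 1-, 3-, and 6-month from CPAP initiation". The Randomization procedure section states: "Randomization will take place after the baseline measurements".

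The Statistical analysis section names a repeated-measures ANOVA and a linear mixed model whose covariance structure is picked by AIC. Its only covariate rule is: "The model will also possibly include some characteristics of patients that are found to influence the level of expected adherence". Those characteristics are to be found by preliminary multinomial logistic regressions. The section does not name baseline AHI, does not say whether the baseline visit is a response or a covariate, and does not say which contrast is tested at 180 days.

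The Procedure section lists the variables used to grade expected adherence as low, moderate or high. They include the "clinical variables (somnolence and apnea-hypopnea index".

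**The concern.** For a continuous outcome measured before and after randomization, the outcome's own baseline is usually the first covariate to fix. Here the plan does state a covariate rule, so this is not merely silence that an analysis plan would fill. The rule is optional, depends on the data, and selects on a link to the adherence class rather than to AHI at 180 days.

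The repeated-measures framework does not cure this by itself. If baseline is one of the responses and arm means are left free at every visit, then with complete data the 180-day contrast is the plain difference in means, and the contrast of changes is the change-score analysis. An ANOVA group main effect that includes baseline also averages in a visit at which randomized arms do not differ in expectation.

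At stake is the width of the confidence interval for a primary outcome, and how far a chance imbalance in baseline severity carries into the estimate. The point is confined to AHI. Hours of CPAP use have no pre-treatment value in patients who have not yet used the device.

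**Working it through.** **Inputs from the protocol** (Sample size calculation; Statistical analysis): 40 per arm, effect size 0.67, two-sided alpha 0.05, power 80%, drop-out 10%. The effect size is given for an apnea-hours difference, not for AHI, so using it for AHI is an assumption.

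**Input not in the protocol:** rho, the correlation between baseline and 180-day AHI. A range is shown.

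**1. The plan's own figure.** A two-sample t-test with d = 0.67, alpha 0.05 and power 80% needs 35.96, so 36 per arm. Then 36 / 0.90 = 40 per arm, 80 in total. The stated number reproduces, and it does so with no credit for baseline adjustment. Power at 36 per arm is 80.1%.

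**2. Variance of the 180-day contrast**, relative to the unadjusted difference, with equal SDs at both visits:
- unadjusted: 1
- change from baseline: 2(1 − rho)
- baseline-adjusted: 1 − rho²

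Since 2(1 − rho) − (1 − rho²) = (1 − rho)², the change score is less precise than adjustment at any rho below 1.

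**3. Results at 36 per arm.** The SE reduction is 1 − √(1 − rho²). Power is from the noncentral t with effect 0.67 / √(1 − rho²) and one degree of freedom lost.

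| Assumed rho | Variance factor | SE reduction | Adjusted power | Gain over 80.1% |
|---|---|---|---|---|
| 0.2 | 0.96 | 2.0% | 81.6% | 1.6 points |
| 0.3 | 0.91 | 4.6% | 83.6% | 3.5 points |
| 0.5 | 0.75 | 13.4% | 89.9% | 9.9 points |
| 0.7 | 0.51 | 28.6% | 97.5% | 17.5 points |

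Gains are taken before rounding. Change-from-baseline power, with effect 0.67 / √(2(1 − rho)), is 65.9% at rho 0.3 and 80.1% at rho 0.5.

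**4. Simulation check** (36 per arm, four visits, 8,000 replicates). SE of the 180-day difference in SD units:

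| rho | Unadjusted | Change | Adjusted |
|---|---|---|---|
| 0.3 | 0.234 | 0.279 | 0.225 |
| 0.5 | 0.236 | 0.237 | 0.206 |
| 0.7 | 0.234 | 0.180 | 0.168 |

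The formula gives √(2 × 0.75 / 36) = 0.204 for the adjusted SE at rho 0.5, in line with the simulated 0.206. Adjustment was the most precise at each rho tested.

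**5. Chance imbalance.** The SE of a baseline difference at 36 per arm is √(2/36) = 0.236 SD. A difference of at least 0.25 SD in either direction has probability 2(1 − Φ(0.25 / 0.236)), about 29%. An unadjusted estimate carries rho times that imbalance.

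**6. If the sample is larger.** The Abstract puts the minimum of 80 in each center, and the Study population section names two hospitals. If these are two centers and are pooled, 2 × 36 = 72 per arm are evaluable. Power at d = 0.67 is then 97.9% unadjusted and 99.6% at rho 0.5, a gain of 1.7 points. The 13.4% SE reduction is unchanged.

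**The case against.** A reader might infer that the plan leaves baseline AHI out of the model, or that it could get in only by accident. The text supports neither. The wording permits patient characteristics as covariates, and the Procedure section makes AHI a named input to the expected-adherence grading, so it is a natural candidate in the preliminary regressions. What can be said is that entry is not assured and would not rest on AHI being the outcome's own baseline.

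The Statistical analysis section names an apnea-hours variable and never clearly assigns a model to AHI. Applying the model to AHI is therefore an inference. This stands, and it is a further reason to write the AHI model down.

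A mixed model that keeps baseline as a response, with arm means constrained equal at that visit, recovers essentially the same precision as a covariate. This also stands; a baseline response is not in itself a fault. The plan does not state the constraint.

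This is a short section of a journal article, and an analysis plan may settle the covariates. Mere silence would indeed be no finding. The point rests on the rule that is printed.

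Finally, if baseline AHI is untreated and follow-up AHI is measured on CPAP, rho may be low and the gain small. That is fair and cannot be resolved from the documents.

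**Conclusion.** The point holds as a loss of precision of unknown size. Baseline AHI is available before randomization, and the plan neither commits to using it in the 180-day AHI comparison nor states a model form that would recover its information.

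It would be wrong to infer bias or an inflated type I error: under randomization the unadjusted and change-score contrasts are both valid. It would be equally wrong to infer that the trial is undersized for this reason, since the stated 80 reproduces without adjustment.

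The gain runs from negligible (rho 0.2 or below) to substantial (rho 0.5 or above). The power figures rest on an assumed AHI effect of 0.67 SD, an assumed rho and 36 evaluable patients per arm; the SE reductions rest on rho alone. The change is worth making because it costs almost nothing at low rho and replaces a discretionary rule in a primary analysis.

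**What to change.** In the Statistical analysis section, state the AHI model separately and pre-specify baseline AHI in it, whatever the preliminary regressions show. Either form will do:

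- AHI at 30, 90 and 180 days as responses in the linear mixed model, with baseline AHI as a fixed continuous covariate on the same scale as the outcome, plus a baseline-by-time term; or
- AHI at baseline and all three follow-ups as responses, with arm means constrained equal at baseline.

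Report the adjusted 180-day group difference with its 95% CI.

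This takes one sentence, written before unblinded analysis. It needs no new data, visits or patients, and uses about one degree of freedom for the 180-day contrast.

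### The covariate screen for the mixed model targets expected adherence rather than CPAP hours, and the model names no center term

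*Protocol article*

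**What the plan says.** The Statistical analysis section plans a linear mixed model with the covariance structure chosen by AIC. Its only sentence on covariates is conditional: the model may include some "characteristics of patients that are found to influence the level of expected adherence identified with preliminary multinomial logistic regressions". It lists no candidate variables, does not define expected adherence, and names no center term.

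Two places in the Procedure section describe an adherence class known at baseline:

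- The first uses socio-demographic, psychological and clinical variables, travel time and comfort with electronic applications to classify "adherence to treatment as low, moderate or high, and to create a tailored motivational treatment plan".
- The second names only two levels, split at a score of 16: "In the case of high adherence (score greater than or equal to 16 on the ESS and CEPCA questionnaires", with scores below 16 counted as low.

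The Randomization procedure section states: "Randomization will be stratified within each center through permuted randomized blocks". It also places randomization after the baseline measurements.

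The Primary outcome section makes mean nightly hours of CPAP use, recorded by the device, a primary outcome together with AHI at 180 days.

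**The concern.** A baseline covariate earns its place in the primary model by explaining variation in the outcome, or by having been used in the randomization. The stated rule uses neither ground. It asks which characteristics go with a predicted adherence level that staff assign from such characteristics. A regression of that level on its own ingredients recovers the assignment rule. It carries no information about the hours the device later records.

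Two further weaknesses follow from the same sentence. Whether any covariate enters, and which, is left open. And the one variable that the design itself marks out for adjustment, center, is not mentioned.

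At stake are the precision of the main comparison and the reader's assurance that its model was fixed in advance.

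**Working it through.** **1. The plan's own figure.** Inputs from the Sample size calculation section: "A sample of 80 patients (40 in each group) will allow detection as a significant effect size of 0.67", alpha 0.05, power 80%, drop-out 10%. The Statistical analysis section makes tests two-sided. The normal approximation gives 2 × (1.960 + 0.842)² / 0.67² = 35 per arm. The noncentral t calculation gives 36 per arm (power 80.05%). Then 36 / 0.90 = 40 per arm, 80 in total. The stated size reproduces, with 72 evaluable patients.

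**2. What the screen finds.** The assumed set-up was 80 patients and six independent baseline variables. A three-level class was formed by cutting the sum of the first five into thirds, and each variable was then tested against the class by multinomial logistic regression at 0.05 (300 runs). The five ingredients were selected in 92–97% of runs. The sixth variable, outside the class, was selected in 6%, which is chance level for a 5% test with 300 runs. The outcome plays no part in this calculation, so the result is the same whichever variable drives CPAP use. The percentages depend on the assumed class; the mechanism does not.

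**3. Type I error.**

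- *The rule as stated.* A screen of baseline variables against a baseline class uses neither arm nor outcome. With n = 72, nine covariates, joint R² 0.20 and covariates kept if associated with the class at p < 0.05 (one-way ANOVA standing in for the multinomial fit, 3,000 runs), type I error was 4.7%.
- *The worst use of the open wording.* Suppose an analyst fitted every subset of zero to three of the nine covariates, and all nine together, and kept the smallest treatment p-value. That is 1 + 9 + 36 + 84 + 1 = 131 models. Type I error was 14.8–15.7% over repeated simulations, against 4.8–5.8% for the unadjusted test.
- *A milder use.* Choosing only between no covariates and all nine gave 6.9%.

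**4. Center.** The number of centers is not given as a figure; two are assumed, from the two hospitals named under Study population. Also assumed are equal center sizes, 1:1 balance within center, 72 evaluable patients, and a share R² of outcome variance due to center. With balance, center does not add to the variance of the treatment difference, but it stays in the residual variance of an unadjusted test. The reported standard error is therefore too large by a factor 1/√(1 − R²), and the size is about 2 × [1 − Φ(1.96/√(1 − R²))]:

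- R² = 0.05: 1.96/√0.95 = 2.011, size 4.4%
- R² = 0.10: 1.96/√0.90 = 2.066, size 3.9%
- R² = 0.20: 1.96/√0.80 = 2.191, size 2.8%

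Simulation with t-tests (40,000 runs per row, standardized difference 0.67 on the total SD):

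| Center share of variance | Size without center | Power without center | Power with center |
|---|---|---|---|
| 0% | 5.0% | 80.1% | 80.1% |
| 5% | 4.6% | 80.7% | 82.1% |
| 10% | 4.0% | 81.2% | 84.0% |
| 20% | 2.9% | 82.6% | 87.8% |

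With center in the model, size stayed at about 5% throughout.

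The Abstract gives a different total: "A minimum sample of 80 participants (40 patients per group) will be recruited in each center". With two centers that would be 160 randomized and 144 evaluable. Power is then about 98–99% with or without center, while size without center is still 4.4–2.8% for shares of 5–20%.

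**The case against.** The strongest reply is that little harm follows from the rule as written. A screen confined to baseline data leaves type I error where it was. A reader might infer from the optional wording that the true error rate is about 15%. The article does not support that: the figure needs a search over 131 models for the best p-value, and no such search is described. It is an upper bound on what the wording permits and does not estimate what will happen.

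The circularity is also inferred. Expected adherence is undefined in the Statistical analysis section and the candidates are unlisted. Gender and civil status, collected under Measures, are not among the stated inputs to the class. This stands as a limit. Still, the low/moderate/high class is the only one in the article that suits a multinomial model. If another class is meant, the screen still aims at something other than the outcome. The inputs may in fact predict CPAP use, but the screen would not be what shows it.

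Two more strong readings fail. One is that the regressions must break down through perfect separation. The cut-off that could cause this belongs to the two-level description, and no cut-off is given for the three-level class. The other is that 20 parameters would be fitted to 80 patients. That assumes one joint model with nine single-parameter predictors, whereas the text speaks of regressions in the plural.

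On center, the article is silent and does not exclude it; a full analysis plan could add it. Omission is conservative, and power stays at or above the planned 80% in every row. This is the weaker half of the point.

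**Conclusion.** The point holds as a modest improvement to the analysis. The stated rule is poorly aimed: on the only reading that the article offers, it returns the classification inputs and cannot identify predictors of CPAP hours. It also leaves the covariates of the primary model undecided. It does not inflate type I error by itself.

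Leaving out center would cost between 1.4 power points (82.1 − 80.7, at a 5% share) and 5.2 points (87.8 − 82.6, at 20%), and nothing at 0%. These figures rest on two equal centers, 72 evaluable patients and assumed variance shares, none of which the article supplies as figures. Nothing here makes the trial invalid or underpowered, and the sample size of 80 is unaffected.

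**What to change.** Delete the preliminary multinomial regressions and the optional wording. Before unblinding, prespecify one covariate set for the primary model: center, baseline AHI and baseline ESS. Where the outcome has a baseline value (AHI, ESS, CEPCA, the well-being scale), include that value as well. Report any other covariate set as a sensitivity analysis only.

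The article gives no evidence of how strongly baseline AHI or ESS predicts CPAP hours, so no gain in power is claimed for them. They are proposed because they are already collected before randomization and can be fixed now.

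Do not use the expected-adherence class as a covariate unless its two descriptions in the Procedure section are reconciled and it is recorded before randomization in both arms. As written, the class serves to build the plan for the experimental arm, so a recorded value for controls is not assured.

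The cost is a wording change and a few degrees of freedom. With two centers and 72 evaluable patients, a single-time comparison goes from 72 − 2 = 70 to 72 − 5 = 67 residual degrees of freedom. No extra patients, visits or measurements are needed.
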